### Retention

The trial intervention period is relatively short, so retention is not expected to be too challenging. It is anticipated that some participants will not wear the CAVA device or have a dizziness attack while wearing the device within 30 days, so the sample size is inflated to allow for this. Some non-conformance will be apparent or self-reported by the participant, others will only be detected once the data is downloaded at the end of the 30 days. Therefore, recruitment will continue until the device data analysis team confirms 255 participants with one qualifying dizziness event or the maximum upper approved limit of 400 participants is reached.

A potential challenge with retention is participants who drop out not returning the CAVA device. As this could impact the rest of the trial, participants are offered a £20 voucher incentive on return of the device and electrodes.

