### Population

We will seek patients with a confirmed diagnosis of one of the three conditions of interest (unilateral MD,^21^ VM,^22^ unilateral posterior canal BPPV^23^ currently experiencing symptoms within 4 weeks prior to recruitment.

Inclusion criteria:

Age 18 and over.Must have relevant index medical condition: Meniere’s: MD, VM, posterior canal BPPV.Experiencing episodes of true vertigo with at least two episodes within the preceding 4 weeks at the time of consent.The vertigo is of a duration and a nature supportive of the relevant index medical condition.It is advisable that participants have access to a phone so they can contact the research team with any issues.Willing to provide informed consent.Willing to comply with the study protocol for using the CAVA device.Willing to complete all study materials.Adequate grasp of the English language or language used within an existing translated version of the informed consent form and patient information sheet and where hospital translators are available to provide support.

Exclusion criteria:

Has an allergy to plasters and/or medical adhesives.Evidence of dermatitis, fragile skin or any other condition that could be aggravated by the repeated application of skin surface adhesives.Pregnant or breastfeeding mothers.Bilateral or second side MD.Active bilateral or second-side posterior canal BPPV.Currently enrolled on an intervention trial (not including questionnaire-based or observational trial).Patients who meet diagnostic criteria for more than one eligible condition at the time of recruitment.

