### Recruitment and screening

255 participants, 85 per target disease, will be recruited from ENT departments, audiology departments and departments of audiovestibular medicine through NHS hospitals. Up to a total of 400 participants may be recruited in order that up to 30 days of data (and/or at least one qualifying dizziness attack with nystagmus) from the device is collected from 255 individuals.

Potential participants will be identified by staff familiar with the trial and the relevant departments in NHS institutions in the UK. Posters will also be used to inform participants of the trial.

Potential participants will be provided with study information either in person or by post/email. They may also be contacted by phone or they may contact the clinical research team directly. All potential participants will be offered the opportunity to discuss the advantages and disadvantages of study participation with a member of the research team and/or their physician before providing consent. See online supplemental materials for a copy of the participant consent form.

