### Intervention

All participants fulfilling the eligibility criteria and providing consent will wear the CAVA device for up to 30 days. To balance the consequences of delaying BPPV treatment with not being able to identify the nystagmus associated with BPPV, individuals with BPPV will be offered a particle positioning manoeuvre after 4 days of wear. The CAVA algorithm will then diagnose each patient based only on the data recorded from the device. The accuracy of the system will be tested by comparing the CAVA system’s diagnosis with each patient’s known diagnosis. The results of the algorithm work (‘the diagnosis’) will not be available until the end of the trial and will not be made available to clinicians or patients during the trial.

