### Sample size

A minimum sample size of 85 participants for each of the three conditions is required to demonstrate a minimum diagnostic sensitivity of 95% and a specificity of 95% with a 3% margin of error for each condition.

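### The pooled reserve and pooled recruitment stop, argued on a 30-day capture window, do not assure 85 evaluable BPPV participants, who are offered treatment after 4 days

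*Protocol article*

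**What the plan says.** All references are to the protocol article.

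- **Sample size:** "A minimum sample size of 85 participants for each of the three conditions is required", in order to show "a minimum diagnostic sensitivity of 95% and a specificity of 95% with a 3% margin of error for each condition". The target is per condition.
- **Recruitment and screening:** 85 per disease, 255 in all. "Up to a total of 400 participants may be recruited" to reach that number. The 400 is not divided between conditions. A participant counts on the basis of up to 30 days of data and/or one qualifying attack with nystagmus.
- **Retention:** some participants are expected either to leave the device off or not to "have a dizziness attack while wearing the device within 30 days, so the sample size is inflated to allow for this". Recruitment runs until 255 participants with a qualifying event are confirmed, or until 400 are recruited. Both limits are totals.
- **Intervention:** everyone wears the device for up to 30 days, but "individuals with BPPV will be offered a particle positioning manoeuvre after 4 days of wear". The section presents this as a balance between delaying treatment and failing to capture BPPV nystagmus.
- **Population:** entry requires "at least two episodes within the preceding 4 weeks at the time of consent". This is the only attack frequency in the article, and it is a minimum.

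**The concern.** The reserve is argued on a 30-day chance of recording an attack. That is the exposure of MD and VM participants. For a BPPV participant who accepts the manoeuvre and responds, the untreated exposure is about 4 days. The Intervention section recognises that early treatment threatens capture in BPPV, but the reserve described under Retention does not reflect it.

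The stopping rule adds to this. Because it counts to 255 in total, surplus MD and VM cases can fill places that the Sample size section reserves for BPPV, and recruitment can close before the ceiling is reached. BPPV is one of the three classes to be told apart. If it ends below 85, its sensitivity is estimated less precisely than planned, while the trial meets its headline number.

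**Working it through.** **The plan's own figure.** No attrition rate is stated, so 400 cannot be derived from the article. It implies a yield of 255/400 = 63.75%, or a loss of 36.25%. Since the article gives no calculation for the 400, there is no arithmetic error to report here.

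**Assumptions (not in the article).** Constant attack rate of k episodes per 28 days; full wear; equal recruitment to the three conditions; MD and VM at k = 2; no BPPV capture after day 4.

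**Capture probability.** P(at least one attack in t days) = 1 − exp(−k·t/28).
- MD and VM, t = 30, k = 2: 1 − exp(−60/28) = 0.883.
- BPPV, t = 4, k = 2: 1 − exp(−8/28) = 0.249. Two other models give 0.257 (daily binomial) and 0.270 (two attacks placed at random in 28 days), so the model matters little.

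**Pooled stop.** With n recruited per condition, recruitment closes when n × (2 × 0.883 + P_BPPV) = 255. Expected values:

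| BPPV episodes per 28 days | 4-day capture | Total recruited at stop | BPPV evaluable | MD and VM evaluable, each |
|---|---|---|---|---|
| 2 | 0.249 | 380 | 31 | 112 |
| 4 | 0.435 | 348 | 50 | 102 |
| 7 | 0.632 | 319 | 67 | 94 |
| 14 | 0.865 | 291 | 84 | 86 |
| 28 | 0.982 | 278 | 91 | 82 |

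For example, at 7: n = 255/(1.765 + 0.632) = 106.4, the total is 319, and BPPV is 106.4 × 0.632 = 67. BPPV is short whenever its capture is below that of MD and VM. The two are equal when 4k = 30 × 2, that is at k = 15. Above that, MD and VM are the conditions that fall short. If MD and VM have 4 episodes per 28 days (capture 0.986) and BPPV has 7, recruitment stops near 294 with about 62 BPPV.

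**If the manoeuvre is declined or does not work.** Let a share s of BPPV participants keep the full 30-day exposure at k = 2, so capture is (1 − s) × 0.249 + s × 0.883. At s = 0.5 this is 0.566, and the pooled stop gives 255/(1.765 + 0.566) × 0.566 = 62 BPPV. At s = 0.62 it is 0.642, giving 68.

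**Stopping by condition within the same 400.** MD and VM each need 85/0.883 = 96.3, say 97, which leaves 400 − 194 = 206 places.
- BPPV at 7 per 28 days: 85/0.632 = 134.5, say 135; total 329, so 85 is reached.
- BPPV at 4: about 196 needed; total 390, so 85 is reached in expectation.
- BPPV at 2: 206 × 0.249 = 51, so 85 is not reached.

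**Precision.** Half-width = 1.96 × √(0.95 × 0.05/n): 4.6 points at n = 85, 5.2 at 67, 6.0 at 51, 7.4 at 33, 7.7 at 31. (The stated 3% margin does not follow from 85 at two-sided 95% confidence. That is a separate matter; 4.6 is the comparator used here.)

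**The case against.** The strongest reply is that the low figures come from assumptions the article does not make.

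- Two episodes in 4 weeks is an eligibility floor. Every participant enters at or above it, and the Introduction describes BPPV attacks as provoked by ordinary head movement, so the real rate may be much higher. At daily attacks the BPPV shortfall is gone.
- The manoeuvre is only offered, and wear may go on to 30 days. Treating day 4 as the end of capture assumes full uptake and immediate success.
- Automatic detection, described under Data analysis, may find nystagmus that the participant did not mark.
- Nothing fixes equal thirds. The pooled 400 already permits unequal recruitment, and the target of 85 per disease suggests that is the intention.
- The reserve also covers non-wear, and the full Clinical Investigation Plan may derive it by condition.

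Most of this stands, and it limits the size of the claim. A reader might infer that an equal BPPV share of 400/3 = 133 will give only about 33 evaluable cases (133 × 0.249) and that the target is out of reach. The article does not support that: it combines the floor used as a rate, an equal split and a fully effective manoeuvre. With 133 recruited, about 7.1 episodes per 28 days would be enough.

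The reply does not remove the problem with the stopping rule. At 7 episodes per 28 days, where an equal share of the full ceiling would nearly suffice, the pooled stop closes recruitment near 319 with about 67 BPPV. An intention to recruit 85 per disease is stated, but the rule that closes recruitment does not enforce it. Nor is this only a detail left out of an article: the stated reserve, treatment time and stopping rule do not fit together.

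**Conclusion.** The concern holds in a limited form. One reserve and one stopping total, both argued on 30 days, do not assure 85 evaluable BPPV participants when BPPV treatment is offered after 4 days. Under the listed assumptions the expected BPPV number at the pooled stop runs from about 31 at the eligibility floor to 91 at daily attacks, and is below 85 for any rate under 15 per 28 days. Non-wear confined to BPPV would lower its number; continued exposure after day 4 would raise it. The article gives no basis for choosing a point in that range, so this is a risk to be closed off and not a predicted shortfall. It also does not show that the 400 is wrongly calculated, and it says nothing on whether the manoeuvre timing is right.

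**What to change.** Keep the ceiling of 400 and the manoeuvre timing. Amend the Recruitment and screening and Retention sections as follows.

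1. Close recruitment separately for each condition once 85 participants with a qualifying attack are confirmed, and pass unused places to conditions still short. Use the same definition of a counted participant in both sections; at present one allows 30 days of data and/or an attack, and the other requires an attack.
2. Derive the expected yield by condition, from the exposure each condition actually has and a stated attack rate and wear rate.
3. Do not fix a split such as 97/97/206 in advance. With 97 recruits and capture 0.883, MD and VM each have only about a 65% chance of reaching 85, and about 3% with 10% non-wear.
4. If a condition is still below 85 at the ceiling, restate its margin for the number evaluable: for example 6.0 points at 51 or 7.4 at 33 (two-sided 95%, sensitivity 95%).

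The cost is a short amendment. Recruitment may run longer and closer to 400, and confirmed cases must be tracked by condition, which depends on timely device downloads. Maximum enrolment and care do not change. If recruitment has already closed (Current study status gives a start in February 2023 and an expected 24 months), only the fourth step and a report of evaluable numbers by condition still apply.

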**Trial registration number:**

ISRCTN81218533, trial protocol V.3.1 (25 January 2024).

Strengths and limitations of this studyThe continuous ambulatory vestibular assessment (CAVA) system is novel in that it records horizontal and vertical eye movements and head accelerations 24/7 and analysis of these signals when they correspond to dizziness symptoms will allow clinicians to retrospectively evaluate the attacks through review of the data.A large number of subjects recruited from centres all over the country will enable the collection of a considerable amount of data for training an artificial intelligence system to diagnose the three conditions listed.The device is technically reliable, comfortable to wear and easy to apply and remove.The CAVA system relies on the patient experiencing an episode of dizziness while wearing the device.The trial is limited to the diagnosis of the three index conditions: Ménière’s disease, vestibular migraine and benign paroxysmal positional vertigo.

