The relationship between balance and eye movements known as the vestibulo-ocular reflex stabilises images on the retina during head movement. When a malfunction occurs in the pathway involving the ears, eyes and brain, an abnormal eye movement is produced, known as nystagmus.^7^ This is characterised by drifting of the eyes in one direction followed by a corrective rapid flick of the eyes in the opposite direction. Different diseases produce different patterns of nystagmus, for example, predominantly horizontal (peripheral vestibular nystagmus), predominantly torsional (BPPV), predominantly vertical (causes outside the peripheral vestibular system).^8^,^10^ The ability to characterise nystagmus will allow us to differentiate between the various vestibular causes of a ‘dizzy attack’ and in the future may provide insights into mechanisms underlying other disorders.

CAVA (continuous ambulatory vestibular assessment) is a wearable device developed to detect nystagmus. As some dizziness can be provoked by the movement of the head,^11^ the CAVA device also records the movement of the head in three axes. The eye movement data captured by the CAVA device is a critical parameter for assessing patients with dizziness.

The CAVA system was evaluated during a clinical investigation involving 17 healthy volunteers. Algorithms were developed to detect physiologically induced nystagmus and achieved an extremely high degree of sensitivity and specificity.^12^ The device was technically reliable, patients were happy to wear it and it was safe.^13^ Participants found the device to be easy to apply and remove and found it to be comfortable to wear. They had little difficulty sleeping while wearing the device and reported that it did not interfere greatly with their daily activities. They did not feel self-conscious wearing the device. From the initial proof-of-concept prototypes, the CAVA device was designed and confirmed to record maximum ocular excursions and eye movements as small as 5 degrees. These tests took place on several subjects with different head shapes, ensuring that recording was not limited by physiological differences or by placement on the face.

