An ML algorithm learns how to adjust automatically its parameters in such a way that it will make measurements on the waveforms that maximise the classification accuracy on the three diseases. Although it would not be obvious what these measurements are, it is possible to analyse the final ML model in such a way that we can later understand what the important criteria for distinguishing between the three diseases are. However, this process requires adequate data. If there is not enough data for the algorithm to learn the correct measurements, we can ‘help’ it by providing it with automatic measurements of features that we think may be important such as slow and fast phase velocities and amplitudes and measured nystagmus frequencies. We are in the process of incorporating these parameters.

Automatic diagnosis tests will be run periodically throughout the active stage of the project to identify potential problems in the data and to check that diagnosis accuracy continues to improve as more data becomes available. The final reported results will represent the diagnostic success rate of the project. The data should prove to be a rich source for further analysis that may considerably increase our understanding of the three target conditions and related matters.

A data validation plan will be developed to describe the downloading, storage and validation of the data in more detail and a statistical analysis plan will be finalised before analysis of the data.

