### Economic evaluation

The health economic plan is to ascertain the NHS, personal and intangible costs involved in previously diagnosed patients versus what they might have required had they worn the device for a period of 1 month’s monitoring. We shall develop an early cost-effectiveness model that will describe both these pathways using the data collected in the study. The effectiveness measure is likely to be obtaining a definitive diagnosis but we shall also allude to quality of life with the disease as a secondary measure of effectiveness when appropriate. We expect the model to be robust using standard probabilistic sensitivity analysis and by obtaining resource use standardised units, values using standard NHS and other unit costs (PSSRU, 2020). We will also collect impacts on personal costs such as out-of-pocket costs, lost wages and income from time-off work and changes to longer-term productivity using standard average UK wage rates.

The economic study will also collect quality of life data using the EQ-5D (3-level) questionnaire to ascertain the short-term and longer-term impact of episodes of dizziness on quality of life. This will inform the design of future clinical trials as well as the preliminary economic model and play an important role in informing whether quality of life is impacted by the different methods of diagnosis.

Data will be collected at each point of patient contact during the monitoring period, collecting data on the resources used and any productivity losses by patients in the preceding days/weeks. Quality of life data using the EQ-5D will be collected at the beginning and at the end of the whole monitoring period. This will help determine the overall quality of life with and without and the frequency of attacks and whether the process of diagnosis itself confers any perceptible changes in quality of life. We shall follow the CHEERS checklist or the Consolidated Health Economic Evaluation Reporting Standards (Husereau, 2022 Drummond M *et al*) in our work.

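### The denominator of the diagnostic success rate is not fixed: the recruitment and algorithm sections imply only participants with a confirmed recorded attack, while other sections imply everyone

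*Protocol article*

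**What the plan says.** All references are to the protocol article; the statistical analysis plan is not shown.

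**Sections that point to evaluable participants only**

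- *Sample size*: "A minimum sample size of 85 participants for each of the three conditions is required". The target behind this number is 95% for both diagnostic sensitivity and specificity, within 3 points, in every condition.
- *Retention*: non-wear and absence of an attack within 30 days are expected, and the sample is inflated for them. Then "recruitment will continue until the device data analysis team confirms 255 participants with one qualifying dizziness event", or the approved maximum of 400 is reached.
- *Data analysis*: the classifier is trained on nystagmus segments labelled with the patient's condition. Diagnosis algorithms are built and tested after those waveforms are confirmed, partly with the team's own detection algorithms.

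**Sections that point to a wider group**

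- *Primary outcome*: sensitivity and specificity are to be given over all participants.
- *Intervention*: the algorithm is to diagnose each patient from the device data.
- *Recruitment and screening*: the 255 are people who supply up to 30 days of data and/or "at least one qualifying dizziness attack with nystagmus". On that wording, a month of recording without an attack can count.

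**How the result is named and may be used**

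- *Data analysis*: "The final reported results will represent the diagnostic success rate of the project".
- *Economic evaluation*: "The effectiveness measure is likely to be obtaining a definitive diagnosis".

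**The concern.** Two different quantities could be reported under the same name. One is accuracy given that the device captured a readable attack. The other is the chance that a patient sent home with the device comes back with a correct diagnosis. The second includes people who did not wear it, had no attack, or had an attack that left no visible nystagmus. Clinicians and commissioners will read an unqualified success rate as the second.

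Two features make the distinction more than semantic. First, whether a participant qualifies is judged by the device data team from the recording itself. An attack that the device fails to show could therefore be replaced and never counted against it. Second, the loss may differ by condition. The Introduction gives the BPPV pattern as "predominantly torsional (BPPV", while the Strengths and limitations list says of the device that "it records horizontal and vertical eye movements and head accelerations 24/7". The Intervention section also offers BPPV participants a manoeuvre after 4 days of wear, and it weighs treatment delay against failing to identify their nystagmus. If capture is lower in one condition, a rate in captured participants hides that.

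**Working it through.** **1. The plan's own figures.** 3 × 85 = 255, which agrees with the stated total. The cap allows 400 − 255 = 145 extra participants, or 145/400 = 36.25% of 400. The 145 is the number of non-evaluable participants at the cap only if 255 qualify; if the cap stops recruitment first, it is more. (The 85 is not reproduced by n = z²p(1 − p)/d² with p = 0.95 and d = 0.03 at two-sided 95%, which gives 203. That is a separate matter and does not affect this point.)

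**2. Who is in the denominator, section by section.**

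| Section | Group implied |
|---|---|
| Retention | 255 with a confirmed qualifying event; others replaced |
| Data analysis | those with confirmed nystagmus waveforms, since others supply nothing to classify |
| Recruitment and screening | 255 with 30 days of data and/or a qualifying attack |
| Intervention | each patient |
| Primary outcome | all participants |

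The Primary outcome wording is attached to nystagmus identification, not to diagnosis, but it is the only sentence that states a denominator for sensitivity and specificity. The rows cannot all describe the same analysis set.

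**3. Size of the difference, as an illustration.** Let a be accuracy in the evaluable, E the number evaluable and N the number enrolled. Counting the rest as not diagnosed,

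proportion correct among all enrolled = a × E / N, and gap = a × (1 − E / N).

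Inputs: a = 0.95 (the Sample size target, used as an assumption), E = 255 (Retention), and N = 300, 350 or 400 (assumed range up to the cap, because no non-evaluable rate is stated). Then a × E = 0.95 × 255 = 242.25.

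| N | E/N | a = 0.95 | gap at 0.95 (points) | a = 0.90 | a = 0.80 |
|---|---|---|---|---|---|
| 255 | 100% | 95.0% | 0 | 90.0% | 80.0% |
| 300 | 85.0% | 242.25/300 = 80.8% | 14 | 76.5% | 68.0% |
| 350 | 72.9% | 242.25/350 = 69.2% | 26 | 65.6% | 58.3% |
| 400 | 63.8% | 242.25/400 = 60.6% | 34 | 57.4% | 51.0% |

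If E is below 255 when N reaches 400, the gap at a = 0.95 exceeds 0.95 × 0.3625 = 34 points.

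**4. A more generous rule.** If the algorithm were forced to name one of three conditions for every non-evaluable participant and were right one time in three, the proportion would be (242.25 + (N − 255)/3)/N: 85.8%, 78.3% and 72.6% at N = 300, 350 and 400. The gap shrinks but remains.

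**The case against.** The strongest reply is that no sentence removes anyone from the accuracy denominator. The Retention text is a rule for stopping recruitment, not a definition of an analysis set, and the statements nearest to a denominator refer to all participants and each patient. Analysis sets are ordinarily left to the statistical analysis plan, which the article says will be finalised before analysis. The stated aim is how far the device's data can separate three conditions, and for that aim accuracy given a recorded attack is a legitimate target. The article lists dependence on an attack during wear as a limitation. It also plans to report compliance, time to first attack and malfunctions, which are parts of yield. Requiring at least two episodes in the preceding 4 weeks favours capture.

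Much of this stands, and it rules out three stronger readings.

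- A reader might infer that accuracy will certainly rest on evaluable participants alone and be overstated by 14 to 34 points. The documents imply that analysis but do not state it, and the points are a scenario: 400 is a ceiling, not an expectation.
- A reader might infer that the device cannot see BPPV attacks. Predominantly torsional is not purely torsional, and the Introduction reports proof-of-concept separation of the target diseases, with motion provocation among the parameters used.
- A reader might infer that the economic model will take the conditional rate as its probability of diagnosis. The article does not say what it will use.

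What the reply does not remove is the disagreement between sections, or the unconditional name given to the result. The analysis plan may settle the analysis set, but the replacement rule operates during recruitment, and its conflict with the Recruitment and screening section is in the text shown.

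**Conclusion.** The point holds as an unresolved denominator with a likely direction of error. Following the Retention and Data analysis sections as written gives accuracy conditional on a confirmed recorded attack with nystagmus. Three other sections suggest a broader group, and the result is named without a condition. If the evaluable-only reading is followed and anyone is non-evaluable, the reported rate will exceed the proportion of device recipients correctly diagnosed.

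The size is not known. The figures of 80.8%, 69.2% and 60.6% assume 95% accuracy, exactly 255 evaluable, and no credit for the rest. Any difference between conditions is plausible from the article's own description, but its size is also unknown. Conditional accuracy is not wrong in itself; the defect is leaving it unlabelled and unaccompanied.

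**What to change.** 1. Reconcile Recruitment and screening, Intervention, Primary outcome and Retention on who counts toward the 255 and who is in the accuracy denominator.
2. Keep the planned estimate, and label it wherever it appears as accuracy given a recorded qualifying attack.
3. Beside it, report the proportion correctly diagnosed among all participants issued a device, overall and for each of the three conditions. Count device not worn, no attack, no visible nystagmus and unreadable data as no diagnosis, and tabulate these reasons by condition.
4. If the economic model uses a probability of diagnosis for the device pathway, take it from the all-participant figure.

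Wear time, diaries, event markers and recordings are already being collected, so no new data are needed. The cost is agreed wording, one extra table, and a second figure that will be less favourable than the conditional one. Making the all-participant figure the sole headline is more debatable given the stated aim, and this point does not require it.
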